### Randomization

The 21 participating clinics will first be divided into two groups based on the poverty level of the catchment area and expected enrollment of individuals with FEP for each clinic. The largest site will be matched with two clinics of a similar poverty level and clinic size as well, as noted above. The matching will be done based on a visual inspection of a scatter plot of expected enrollment by the income of each site. Then, blocks of size 2, and one block of size 3, will be randomly generated. Randomization will be performed using a randomization scheme generated by SAS 9.4. This procedure will entail (1) generating a random number 0 or 1 ten times, and (2) assigning 0 to the Usual FEP care clinic and 1 to the OTCH clinic in each matched pair. For the block of size 3, two sites will be assigned to either OTCH or Usual FEP care, and the remaining site to either OTCH or Usual FEP care as well. The statistician will notify the contact-PI once the randomization is done, and he will then call the CMHC Director to inform him/her of the assigned treatment status, followed by a written note to the Director with the same information. The random allocation within blocks of two will enable us to bring into the study one OTCH and one Usual FEP Care CMHC per month. We note that the randomization (and notification) will be done at the start of the project, which will enable us to select equal numbers of OTCH and Usual FEP Care CMHCs for data collection (at organizational, provider, and participant level) during the preparatory phase.

### Inclusion/exclusion criteria

Study inclusion criteria for clients are (1) verified as having FEP by a psychiatrist in a mental health clinic within 2 years of the onset of psychosis; (2) meet ICD-10 criteria for a diagnosis of schizophrenia, schizophreniform, schizoaffective disorder, delusional disorder, brief psychotic disorder, or psychosis not otherwise specified; (3) 15–35 years old; (4) have the capacity to provide fully informed consent (for those under 18, assent plus informed consent of parent/guardian); and (5) able to participate in research assessments in Spanish. In order to conform with government legislation, individuals will be deemed ineligible if they have a non-psychiatric medical condition that impairs functioning, a psychosis due solely to another medical condition, or a developmental disability. All subjects aged 18 years or older will be required to provide written informed consent for study participation. Subjects under 18 will provide written assent and their parent/guardian written consent. As noted above, we will also enroll providers, who will be mental health workers who have direct contact with FEP clients. Of note, these two groups (clients and providers) will be recruited at both OTCH and Usual FEP care sites to assess the implementation outcomes included in this cluster RCT (i.e., fidelity, acceptability, and uptake).

For the qualitative assessments, we will interview clients enrolled in the cluster RCT, plus policy makers and health directors. These will be individuals who are 18 years of age or older and employed full- or part-time at public agencies or participating clinics, respectively. Finally, we will also interview family members, who will be individuals who live with or are close to the client, and who are involved in providing support.

### Interventions: OTCH vs usual FEP care

#### OTCH

We will adapt the OTNY model to the Chilean cultural and service context to create OTCH. OTNY, as previously noted, is an intensive outpatient program for young people who have experienced their first episode of psychosis. The program is implemented by a multidisciplinary team with specialized training, who provide coordinated evidence-based treatments based on the interests, needs, and preferences of each participant. The program emphasizes assertive outreach and engagement and is offered for an average of 2 years.

OTNY teams offer participants a range of evidence-based treatment options, including individual therapy based on Cognitive Behavioral Therapy (CBT) for psychosis, psychiatric medications, family education, and support, supported education and employment, case management and community support, and a focus on physical wellness and coordination with primary health. OTCH teams will be able to offer all of these services, some of them with low availability in the country (e.g., CBT), except peer support since clinics are not staffed with peer specialists. Services are delivered in a person-centered, recovery oriented, culturally competent manner that prioritizes an individual’s needs and treatment preferences using shared decision-making [13]. The overarching goal is to help participants achieve personalized goals typically related to school, work, and relationships. The program strives for a balance between encouraging independence and offering support when needed [13]. An OTCH team will be comprised of five members however, adaptations will be made to how the roles will be carried out by the respective team members in response to the local context (Table 1).

**Table 1 Tab1:** OTCH team roles

Role	Description
Team coordinator (TC)	A mental health professional, selected by a health director/manager, who will oversee the OTCH team and ensure that all team members adequately fulfill their roles.
Primary clinician (PC)	Preferably a psychologist, who will be the primary resource for the participant and his/her family and responsible for formulating the treatment plan in accordance with the participant’s preferences and coordinate the execution of the treatment plan with the rest of the team. This professional will also deliver psychosocial interventions to participants and family education and support. Some teams may have more than one professional fill this role.
Community support professional (CSP)	Preferably an occupational therapist, who will provide supported employment and/or education and connect the participant with peers and community resources. In the OTNY model, this role is known as the “supported employment and education specialist.” The name change for OTCH reflects an expansion of this role in the Chilean adaptation.
Prescriber	A psychiatrist, who will provide medications and symptoms management using shared decision-making and an evidence-based prescribing approach.
Nurse	Either carried out by a nurse or a nursing technician, who will support the psychiatrist and monitor medication use and side effects, facilitate individual and group wellness sessions, monitor physical health and vital signs, and coordinate with primary care.

Delivery of OTCH services will be done using a phased approach; for details on each phase see Table 1. At the beginning of treatment, a participant will be assigned a Primary Clinician (PC) by the Team Coordinator (TC) and meet with the PC, and ideally the Prescriber, for an initial orientation session. During this initial phase, team members focus on engaging with participants and families, assessing their needs, and helping the individual begin identifying goals. Because no part of the model is compulsory, program participants will be encouraged to use shared decision-making to identify treatment areas to prioritize. Even if a participant decides not to take medication, he/she will still be encouraged to meet with the Prescriber and Nurse even if infrequently. For instance, participants should meet with the PC and Prescriber/Nurse once a week for the first month (the prescriber and nurse will alternate weeks) and then every 2 weeks thereafter. Meetings with the Community Support Professional (CSP) will depend on each participant’s goals, interests, and preferences. This person-centered, recovery-oriented approach is crucial to foster engagement with services within and outside OnTrack.

The second phase constitutes the bulk of the 2-year program. Once a strong relationship has been established with the participant and family and individualized goals have been defined, team members will provide interventions focused on helping individuals achieve their goals and promote their recovery as well as deliver core sessions providing psychoeducation about FEP, its course, treatment and information to support recovery and resilience to participants and family members. During this time period, meetings with the PC, Prescriber/Nurse, and other team members will continue to happen as frequently as needed depending on the interventions being delivered and participant/family preferences. As participants start reaching goals and becoming more involved in community and school/work activities it is typical that meetings with team members decrease in frequency. The final phase begins six months prior to discharge from the program and is focused on understanding the participant’s achievements, and the identification of future needs to determine connection to long-term services.

The intervention is offered in a flexible manner, responsive to the needs and preferences of each participant which helps to limit disengagement from services. If participants decide that they do not want to take engage in any part of the model, the services offered will be modified to meet this request. Participants should not receive other concomitant psychiatric treatment during the time that they are receiving care from the OTCH team because the interventions provided by the team are comprehensive and should treat primary psychosis and other psychiatric comorbidities. Criteria for discontinuation of the intervention would be based on clinical judgment indicating that (1) the diagnostic presentation has changed, and the individual has a different psychiatric disorder requiring different services or (2) the worsening of symptoms requiring a different level of care such as inpatient hospitalization. Furthermore, if a participant decides that they no longer want to receive services from the OTCH team, an appropriate referral and linkage will be made either to another service within the community mental health center or to another mental health service provider (Table 2).

**Table 2 Tab2:** Typical activities of each phase of the intervention

Phase 1: Engagement and needs assessment (Months: 1–3)	Phase 2: Ongoing intervention and monitoring (Months: 3–18)	Phase 3: Transition (Months: 18–24)
Activities: • Introduction to all team members • Description of OTCH program • Intake assessment • Needs assessment (e.g., housing, income, etc.) • Risk and trauma assessment • Building rapport and getting to know the participant and their support network • Identification of individual goals (e.g., employment, education, relationships) • Introduction of shared decision making • Deciding on level and type of family involvement • Development of a treatment plan	Activities: • Delivery of core psychoeducation sessions • Delivery of psychosocial interventions to help achieve goals and build resiliency (e.g., social skills training, CBTp, substance use treatment, illness self-management, coping skills, and behavioral activation) • Suicide prevention • Review and revise treatment plan • Actively pursue work and school goals • Delivery of psychoeducation and support to family • Relapse prevention • Explore transition readiness	Activities: • Determine gains made and goals attained • Decrease frequency of services delivered • Develop a transition plan • Identify and connect to mental health services in the community • Identify and connect to community-based supports • Engage family in transition plan and identify their role • If possible, test whether these new services align with participant’s preferences

### Training and supervision

The training approach for the OTCH teams will follow the established training strategies utilized by the OnTrack Central training team at the Center for Practice Innovations, for training teams in the state of New York and nationally [18]. The training will be delivered primarily through an online learning platform that will allow for virtual meetings focused on individualized and group consultation and coaching, didactic webinars, opportunities for sharing and learning from each other, and discussing data to help maximize the quality of the implementation. The OTCH trainers will also be available via email or phone for specific consultation needs that arise over the duration of the program and they will have access and regular meetings with OnTrack Central trainers in New York to help adapt the training strategy to meet the local needs.

OTCH teams will receive an initial, remote training providing a general overview of the treatment model before starting implementation. This allows for an opportunity to discuss practical components of the implementation, understand where each team is at regarding their readiness for implementation of the treatment model and provides an opportunity for engaging in in vivo problem solving to address questions and barriers faced at the individual agencies hosting the programs. Training then continues following a set monthly schedule of role and team-based learning collaborative calls, so that each team receives the same amount of training and information on a regular basis (Table 3). Learning collaboratives have traditionally been used in health care and are increasingly used in behavioral health care [18]. Fundamental elements of a learning collaborative include a number of organizations working together, using quality improvement methods to close the gap between potential and actual performance, learning from experts as well as from one another, and using data to track performance [18]. This will be complemented with resources for self-paced learning that teams can access through the virtual learning platform. Trainers and trainees will also receive site-level data (both related to outcomes and fidelity) that will be utilized during virtual meetings to guide discussions focused on improving the implementation, clarifying questions related to the model, and problem-solve challenges they may be facing.

**Table 3 Tab3:** Description of training approach

Training event	Description
Initial Implementation Calls	Consists of individual phone calls which provide an opportunity for the agency leadership and the team leader to develop a strategy for forming the team and identifying the agency-level infrastructure that needs to be in place to ensure good team functioning.
Synchronous and Asynchronous Initial Training	Consists of a 3-month training period where individuals will be assigned materials for self-paced learning and then will join a monthly videoconference meeting. Training will consist of a general overview of the treatment model and all of its components delivered before starting implementation of OTCH.
Individual role-based videoconference meetings	Consists of monthly learning collaborative virtual meetings facilitated by a trainer focused on the implementation of specific elements of the role and give providers an opportunity to learn from each other’s experiences
Care consultation videoconference meetings	Consists of monthly virtual meetings attended by two entire teams and at least two trainers focused on discussing a program participant in detail and getting advice and feedback
Special topic webinars	All teams are invited to receive training on a specific topic requested by trainees (e.g., prescribing long-acting injectable medications, cultural competency, and suicidality). These will take place as needed.

#### Usual care

The FEP policy will ensure that participants from the control sites will have access to Usual FEP Care. This is generally provided in mental health outpatient clinics, which (i) serve a population enrolled in the public health care system, (ii) provide services such as psychiatric medication, psychotherapy, and psycho-education for people with FEP and their families, and (iii) have a diverse team of professionals that include psychiatrists, psychologists, psychiatric nurses, social workers, occupational therapists, and family counselors. The services offered in these clinics, however, tend to have some limitations, three of which are relevant to this trial.

First, these clinics offer services to clients with a wide range of mental health conditions, not just those with FEP, and therefore, providers lack specialized training on treating FEP (e.g., evidence-based prescribing of antipsychotic medications or evidence-based psychosocial approaches). Second, recovery-oriented services based on shared-decision making and person-centeredness are rarely offered in these clinics since a more biomedical model of care tends to be used. Third, they tend to have minimal resources to provide services in the community and often face several challenges in delivering coordinated care between different types of services (i.e., primary care, other specialized mental health services, and emergency services) and likely across professionals in a team-based model.

### Recruitment

Given the current COVID-19 pandemic, most research and intervention procedures will be conducted remotely, but there might be some exceptions as described below. This was decided after consulting with local stakeholders, including providers from the participating clinics, who noted that many clinics are providing mental telehealth services via telephone, email, and video conferencing. Considering that most people in Chile have smart phones, this will be the method of choice to contact, interview, and follow up potential participants via either telephone or Zoom/Webex calls.

After a site enters the study, the participating clinic will be asked to refer all individuals with FEP to our study team. A health provider in each of the participating clinics will be designated to be the local point person for the coordination of recruitment and follow-up of study participants in his/her site; this role will be referred to as “Local Coordinator.” As noted previously, an FEP registry is in place in Chile to identify individuals with an FEP to ensure they receive timely and appropriate treatment. The Local Coordinators can use that database to identify potential participants at their clinics. Using this tool, the Local Coordinator will assign a numeric screening ID number to each potential participant and maintain a log with this information in a secure cabinet in each site. Each site will be assigned a numeric range (1000s, 2000s, 3000s, etc.). The Local Coordinator, who is not part of the OTCH research team, will contact the potential participants by phone, videoconference, or in-person when possible. If verbal consent is obtained, the Local Coordinator proceeds with a brief introduction to study. The Local Coordinator will briefly explain that he or she can participate in a research study and will describe the study’s purpose. If the client accepts to participate, the Local Coordinator will notify a member of the Research Team, known as the Registration Designee, who will oversee assessing the capacity of consent and administering the informed consent form. If someone serves as a Registration Designee for the participant, this person will not be allowed to serve as an interviewer for this participant in order to maintain the blind. This process will take place remotely unless the clinic is open for in-person appointments. Once consent is obtained, an interviewer will be notified so he/she can contact the potential participant and conduct the baseline assessment. Similar procedures will be followed for minors, and for providers, policy makers, health directors, and family members who participate in the study.

Following the recommendations by McRae et al. [17] and Giraudeau et al. [18] on administering consent forms in cluster RCTs, there will be two different consent forms: one for participants from intervention clinics and another one for participants from controls clinics. In addition, we will have other consent forms for policy makers, health directors, providers, and family members.

Interviewers who conduct both the clinical assessments and qualitative interviews will be mental health professionals with prior research training and experience conducting clinical assessments. They will be trained on research and assessment procedures by the Research Team through 3 on-line, videoconferencing sessions. The first session will entail going over the research protocol and the interviewer’s manual. The second session will address the required procedures to enter data into RedCap and report adverse events. Finally, in the third session, a thorough review of the quantitative and qualitative measures will take place, with special emphasis in the administration of the clinical-based measures such as the PANSS.

The risks to participants are minimal, and the measures we will take, combined with rigorous team training, will reduce them even further. In case of emotional upset and/or suicide feelings, immediate action will be taken, such as a referral for mental health and suicide risk assessment and appropriate counseling at usual health services in Chile.

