#### Aim 2a and 2b analyses

We hypothesize that the OTCH program will be effective and that, over time, user-level psychotic symptoms, functioning, and recovery orientation will improve. Tests for treatment differences between the intervention arms on each outcome (symptoms, functioning, and recovery orientation) will be performed using an HLM including an indicator for intervention status, time (baseline, 12, 24 months), and intervention*time. The magnitude and statistical significance of the beta coefficient for the interaction will provide an assessment of the extent to which the change in psychotic symptoms, functioning, and recovery orientation since baseline over time differs by intervention arm.

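### Clinic staff identify and approach clients after allocation is disclosed, so the arms may differ in time already in care, and the conditional covariate adjustment does not deal with this

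*Protocol article*

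**What the plan says.** **Allocation and disclosure.** Under Randomization: "We note that the randomization (and notification) will be done at the start of the project". Once the scheme is generated, the contact investigator learns the result and "he will then call the CMHC Director to inform him/her of the assigned treatment status". Clinics are matched on catchment poverty and expected enrolment only.

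**Who recruits.** Under Recruitment, after a site has entered: "A health provider in each of the participating clinics will be designated to be the local point person for the coordination of recruitment". This Local Coordinator is outside the research team, "will contact the potential participants by phone, videoconference, or in-person when possible", and introduces the study. The research team comes in only after the client has accepted. Consent forms differ between intervention and control clinics.

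**From which pool.** The same section says "the participating clinic will be asked to refer all individuals with FEP to our study team". Of the national FEP register it says "The Local Coordinators can use that database to identify potential participants at their clinics". The coordinator gives each candidate a screening number and keeps a log. Under Inclusion/exclusion criteria a client must be "verified as having FEP by a psychiatrist in a mental health clinic within 2 years of the onset of psychosis". Entry is not limited to new cases.

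**Analysis.** Aim 2a tests whether "the change in psychotic symptoms, functioning, and recovery orientation since baseline over time differs by intervention arm". The Aim 1 models use 12 and 24 months as the time points. Under Aim 1, adding a covariate will be weighed if descriptive analyses show baseline differences. Table 4 lists DUP, from onset to the start of clinic treatment as recorded in the register, as a moderator.

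**The concern.** Randomising clinics balances, in expectation, what exists when clinics are randomised. It does not balance clients who are found later by people likely to know the arm. If the clients approached differ between arms in how long they have been in treatment, that difference was not created by OTCH but enters the comparison.

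Time in care plausibly matters for both sets of outcomes. Recently presenting clients and clients already in treatment for many months need not have the same expected course over the next 24 months, which bears on Aim 2a. Clients already established in care have shown that they attend, which bears on retention and adherence among the primary outcomes. The protocol collects no variable that states time in care, and its adjustment rule depends on what the descriptive tables happen to show.

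**Working it through.** **1. Order of events.** Clinics are randomised and directors told; sites enter; a clinic provider identifies and contacts clients; clients accept; the research team takes consent on an arm-specific form. Selection into the sample therefore follows disclosure. The only blinding step described within recruitment keeps the person who takes consent from also interviewing that client. It does not cover the person who finds clients.

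**2. Does analysing change remove the problem?** Let p1 and p0 be the shares of newly presenting clients under OTCH and usual care, and gN and gE the expected change in new and established clients with no OTCH effect. Then

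expected arm difference in change = (p1 − p0) × (gN − gE).

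A constant difference in baseline level cancels; this product does not. Its sign depends on which arm holds more new clients. For Aim 1 the stated time factor has no baseline occasion and no baseline term is fixed, so a difference in level, for example in adherence, can also pass into the contrast.

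**3. Does DUP stand in for time in care?** DUP = treatment start − onset. Time in care = enrolment − treatment start. If enrolment falls within 24 months of onset, a client with a DUP of x months can have anything from 0 to 24 − x months in care. If the eligibility wording dates the psychiatrist's verification and not enrolment, the range is wider. Equal DUP in the two arms is thus compatible with very different time in care. The treatment-start date needed for DUP is, however, the same date needed for time in care.

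**4. Size.** The protocol gives no figure for this bias. Its nearest figure, under Sample size and power analysis, is 80% power for d = 0.35 with 270 participants, 21 clinics, intra-class correlation 0.05 and two-sided alpha 0.05.

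- Mean cluster size: 270/21 = 12.86.
- Design effect: 1 + (12.86 − 1) × 0.05 = 1.593.
- Effective N: 270/1.593 = 169.5.
- Standard error of the arm difference: √(4/169.5) = 0.154 SD.
- Power at d = 0.35: Φ(0.35/0.1536 − 1.96) = Φ(0.32) = 62.5%, so the stated 80% is not reproduced. That is a separate matter. The standard error that 80% power implies is 0.35/(1.96 + 0.84) = 0.125.

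Illustration, with values the article does not give: a 20-point difference in the share of new clients and 0.5 SD more improvement in new clients without OTCH.

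- False effect: 0.20 × 0.5 = 0.10 SD, which is 0.10/0.35 = 29% of the design effect.
- Rejection when the true effect is zero: 0.10/0.1536 = 0.65, so Φ(0.65 − 1.96) + Φ(−0.65 − 1.96) ≈ 0.095 + 0.005 = 10%. With the standard error of 0.125: 0.10/0.125 = 0.80, so Φ(−1.16) + Φ(−2.76) ≈ 0.123 + 0.003 = 13%.
- In the opposite direction, a true 0.35 would appear as 0.25, and power would fall from 62.5% to Φ(0.25/0.1536 − 1.96) = Φ(−0.33) ≈ 37%.

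Range: imbalances of 10 to 40 points and extra improvement of 0.3 to 0.9 SD give false effects of 0.03 to 0.36 SD and rejection rates of 5.4% to 65%. So wide a range shows only that the article does not determine the size.

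**The case against.** The strongest reply is that the article already asks every clinic, in both arms, to refer all its FEP clients. By law anyone under evaluation for FEP is entered in the register (Background), and the log is described as built with that tool. The permissive wording may mean only that coordinators have access. This largely stands: a sampling frame and a log exist, and a reader should not infer that coordinators are free to pick whom they like. What remains is that the request and the permission do not say the same thing, and no reconciliation of the log with the register is described.

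Second, the article does not say that coordinators know the arm. That is right; it is an inference from the director being told, the OTCH team being trained before it starts, and the consent forms differing. Such knowledge is hard to avoid when a clinic-wide service is randomised, which is a reason to protect the recruitment step.

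Third, a marked difference in case mix might show in baseline symptoms, functioning, adherence or DUP and so trigger the covariate rule. It might, but that rule only commits to considering a covariate, is written under Aim 1, and cannot flag a variable that has not been derived.

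Fourth, a condensed article may leave recruitment detail and covariates to fuller documents. Here, though, recruitment is set out step by step, down to the numbering of screening IDs, and the conditional adjustment is a stated rule. The point concerns what is stated.

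A reader might also infer that the bias favours OTCH. The documents do not support that. If OTCH clinics enrolled newer clients and usual-care clinics enrolled established attenders, symptom change could favour OTCH while retention and adherence ran against it, and nothing says that this pattern, and not its reverse, would occur.

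**Conclusion.** The point holds as a risk that the design leaves open and the planned analysis does not reliably detect or remove. It rests on three things in the text: disclosure before recruitment, clinic staff making the identification and first approach, and a pool mixing new and established cases. It rests on one inference, that coordinators know the arm.

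Its direction and size are unknown. The 0.10 SD and 10% figures illustrate sensitivity under assumed values and are not estimates. The article's PANSS figure of 0.91 cannot fill the gap: it is improvement among people enrolled in a treatment programme, so it does not separate natural course from programme effect. The finding is that time in care could differ by arm and would not be seen, not that the trial will show a false benefit.

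**What to change.** 1. **Recruitment, both arms.** State that the FEP register is the list of candidates, so that the register sentence agrees with the request to refer everyone. Enter the outcome of each approach in the existing log. No fixed order of approach is needed.
2. **Analysis.** Derive time from treatment start, already drawn from the register for DUP, to enrolment. Prespecify it, with its interaction with time, as a covariate in the participant-level Aim 1 and Aim 2 models, in place of the conditional adjustment.
3. **Reporting.** Give the numbers registered, approached and enrolled, and the distribution of time in care, by arm.

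The trial status section dates recruitment from March 1, 2021 to an expected December 1, 2022. Items 2 and 3 can therefore cover every participant, while item 1 can cover only the recruitment that remains. The cost is one added covariate and a little record-keeping. The limit is that adjustment handles the measured difference in time in care and not selection on characteristics that nobody records; the counts in item 3 let readers judge how much of that may remain.
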